## Abstract

**Background:**

MELD-based allocation for liver transplantation follows the “sickest-patient-first” strategy. The latter patients present with both, decreased immune competence and poor kidney function which is further impaired by immunosuppressants.

**Methods/Design:**

In this prospective observational study, 50 patients with de novo low-dose standard Advagraf®-based immunosuppression consisting of Advagraf®, Mycophenolat-mofetil and Corticosteroids after liver transplantation will be evaluated. Advagraf® trough levels of 7-10 μg/l will be reached at the end of the first postoperative week. Immunostatus, infectious complications, graft and kidney function are compared between patients with a pretransplant calculated MELD-score of ≤20 and >20. Each group comprises of 25 consecutive patients. Prior to liver transplantation and on the postoperative days 1, 3 and 7, the patients’ graft function (LiMAx test) will be evaluated. On the postoperative days 3, 5 and 7 the patients’ immune status will be evaluated by the measurement of their monocytic HLA-DR status.

Infectious complications (CMV-reactivation, wound infection, urinary tract infection, and pneumonia), graft- and kidney function will be analysed on day 0, within the first week, and 1, 3, 6, 9 and 12 months after liver transplantation.

**Discussion:**

This study was designed to assess the effect of a standard low-dose Calcineurin inhibitor-based immunosuppression regime with Advagraf® on the rate of infectious complications, graft and renal function after liver transplantation.

**Trial registration:**

The trial is registered at “Clinical Trials” (http://www.clinicaltrials.gov), NCT01781195.

## Background

Liver transplantation (LT) is the only curative treatment for patients with decompensated liver cirrhosis. The model for end-stage liver disease score (MELD-score) is used for the prioritization of patients awaiting LT [1].

The MELD-score was initially developed to evaluate the prognosis after transjugular intrahepatic porto-systemic shunt (TIPS). The laboratory parameters creatinine, bilirubin, and international normalized ratio (INR) are needed for calculation of this score [1]. Nowadays, the MELD-score is also used to allocate grafts for LT. The calculated MELD-scores of patients waiting for LT usually range between 6 and 40 [2].

Sawitzki *et al.* described markers that could be used to determine a patient’s immune status. This would make it possible to tailor the extent of the individual’s immunosuppression therapy after LT. However, the lowest possible dose of immunosuppressant needs to be determined individually in order to minimize side effects of immunosuppression while also avoiding an increase in the rejection rate [3]. The patient’s immune status can be evaluated by the measurement of B-cell sensitization and soluble biomarkers like CD30 [4,5]. In addition, the immune status after LT, sepsis, injuries, and surgery can be evaluated by the monocytic HLA-DR status. A decreased monocytic HLA-DR status is indicative of an impaired immune competence [6].

In this context, it would be interesting to investigate to what degree a patient’s HLA-DR status corresponds to the labMELD-/Na-MELD-score and to measure the liver function with the LiMAx test. Furthermore, this trial aims to assess whether or not high-MELD patients (MELD-score >20) can benefit from a low-dose, prolonged-release immunosuppression with Advagraf®.

HLA-DR belongs to the major histocompatibility complex (MHC)-II family and is important for antigen presentation to CD4 + -T-cells [6,7]. Monocytes express HLA-DR on their surface, which can easily be detected by flow cytometry [6]. As mentioned above, the monocytic HLA-DR status has been used to evaluate the immune status after surgery, trauma, or during sepsis [6]. Moreover, the decreased monocytic function found during sepsis may be due to a diminished HLA-DR expression [8].

Granulocyte-Macrophage Colony-Stimulating-Factor (GM-CSF) activates monocytes and prevents apoptosis, in addition, GM-CSF increases monocytic HLA-DR expression [8]. Havemann *et al.* measured the monocytic HLA-DR status after LT in 20 patients and reported that a decreased monocytic HLA-DR status was associated with the risk of sepsis after LT. The risk of sepsis increases with the administration of an elevated Prednisolone dosage [7,9]. Administering reduced doses of Prednisolone may prevent patients with decreased monocytic HLA-DR statuses from becoming septic [7].

In order to allow for multi-center trials on the monocytic HLA-DR status and in an effort to index a patient’s immune status, a standardized BD Quantibrite™ HLA-DR/monocyte reagent was developed by Döcke *et al.*[6]. For consistent results, the blood should be stored on ice in EDTA tubes and must be analyzed within 4 hours after extraction [6].

The LiMAx test is useful for pre- and postoperative examinations of patients undergoing extensive liver resections to determine both, the risk of postoperative liver failure and liver function. The same applies to patients after LT [10]. The LiMAx test is usually done at the patient’s bedside. Patients are required to lay in bed and avoid eating or smoking within 3 hours prior to being given ^13^C-Methacetin infusion. The enzyme CYP1A2 is exclusive for hepatocytes and metabolizes ^13^C-Methacetin to Paracetamol and ^13^CO_2_. Thus the ^13^CO_2_/^12^CO_2_ ratio in the exhaled air correlates with liver function [11].

Unlike the LiMAX test, the sole use of laboratory parameters (e.g. bilirubin, ammonia, INR, and glutamatdehydrogenase) is not optimal for analyzing patients’ graft function, since bilirubin levels are dependent on preoperative levels and indicate transplant failure with a delay of a few days. An increased INR can also be found as a consequence of bleeding, disseminated intravascular coagulation (DIC) or as a side effect of several medications [10]. Early recognition of graft dysfunction is necessary as hepatic dysfunction affects metabolism and elimination of Tacrolimus with the need of future dose adjustments [12].

Since the MELD-score is often used for graft allocation before LT and the underlying laboratory values are dependent on the methods used at the time of measurement, it is possible for the MELD-scores to vary significantly among the different laboratories [13,14]. It would be interesting to investigate the correlation between the pre-operative MELD-score and the LiMAx results, and determine whether or not this correlation has any influence on the patient’s preoperative immunostatus (HLA-DR status).

At our institution, a Tacrolimus-based immunosuppression (Advagraf®, Prograf®) belongs to the standard immunosuppression for patients undergoing LT.

Negative side effects of Calcineurin inhibitors (CNI) are, among others, renal impairment and infectious complications [15]. High-MELD patients often present with a limited renal function as creatinine is one component of the MELD-score [1]. The combination of CNI application and higher MELD-scores increases the risk of renal impairment [15]. Furthermore it has been hypothesized that high-MELD recipients have decreased immune competence [16] and can therefore benefit from the lowest possible doses of immunosuppressant drugs after LT. Low-dose Advagraf® with aimed trough levels of Tacrolimus at the end of the first week after LT should protect patients, especially high-MELD patients, from negative side effects of CNI, especially with regard to renal function and infection rate, while simultaneously promoting no increase in the rate of rejection. Furthermore, it is assumed that patients with a MELD-score ≤20 also benefit from this immunosuppressive regime.

The aim of this study is to evaluate the effectiveness of a low-dose Calcineurin inhibitor-based immunosuppressive regime with Advagraf® where aimed trough levels of Tacrolimus are reached at the end of the first week after liver transplantation, in regard to infectious complications and both, graft and renal function.

## Methods/Design

### Study population

The study population consists of patients scheduled for LT for any indication. Inclusion criteria are age of >18 years and <65 years, first transplantation, initial immunosuppression with Advagraf®, Corticosteroids, and Mycophenolat-mofetil (MMF) with surgery and immediate postoperative treatment in the Department of General-, Visceral- and Transplant Surgery at the University Hospital of Heidelberg.

Exclusion criteria are missing written consent, re-transplantation, and the presence of acute infections (CMV-reactivation, pneumonia, urinary tract infection, wound infection, and reactivation of hepatitis B/C). The individual criterion for discontinuation is the patient’s withdrawal of written consent.

The study protocol has been approved by the ethics committee, University of Heidelberg (S-577/2012).

### Study objectives

The primary objective is to evaluate the rate of infectious complications in the surrounding of pre-existing reduced immune competence in patients after LT under standard CNI-based immunosuppression with Advagraf®, MMF and Urbason (Table 1).

**Table 1 T1:** Immunosuppression regime

*Urbason*	Day 0:	2 × 125 mg i.v.
	1. POD	2 × 80 mg i.v.
	2. POD	2 × 40 mg i.v.
	3. POD	2 × 20 mg i.v.
	4. POD	1 × 40 mg i.v./p.o.
*MMF*	2 × 1 g/day	Start within 12 h after LT
*Advagraf®*	1 × 0.1 mg/kg/day	Start within 12 h after LT; aimed trough level at the end of the 1st week 7-10 μg/l

i.v. = intra-venous, MMF = Mycophenolat-mofetil, p.o. = per os, POD = Postoperative day.

Patients with grafts from CMV- positive donors receive standard CMV-prophylaxis (Table 2).

**Table 2 T2:** CMV-Prophylaxis

CMV- positive donor	Valganciclovir for 3 months:
	- 2 × 450 mg/d per os during the 1st and 2nd week after LT
	- 1 × 450 mg/d per os thereafter
	- Reduced dosages in case of renal dysfunction creatinine clearance (ml/min):
	- 40-59: 1 × 450 mg/d
	- 25-39: 450 mg every 2^nd^ day
	- 10-24: 450 mg 2x/week
	- Patients under dialysis: 450 mg 2x/week
	Ganciclovir i.v.:
	- 2x/d 5 mg/kg
	- Reduced dosages in case of renal dysfunction creatinine clearance (ml/min):
	- 49-10: 1x/d 2,5 mg/kg
	- <10: 1,25 mg/kg 2x/week
	- Patients under dialysis: 1x/d 1,25 mg/kg

As secondary parameters the correlation between the patients’ preoperative HLA-DR statuses, MELD-scores and liver functions measured by the LiMAx-Test and the correlation between the patients’ postoperative HLA-DR statuses and liver function measured by the LiMAx-Test will be assessed. Furthermore infection rate, graft- and kidney function over time will be analysed and compared between the two groups.

Clinically relevant measures of liver function (serum bilirubin, INR, serum transaminase peaks) and kidney function (creatinine, glomerular filtration rate (GFR)) as well as episodes of rejection will be documented.

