### Design and trial flow

For participation in this prospective, mono-centric observational study, informed written consent is mandatory. We will evaluate 50 patients, including 25 consecutive patients with a calculated pretransplant MELD-score of >20 and 25 consecutive patients with a calculated pretransplant MELD-score of ≤20. Infectious complications (CMV-reactivation, wound infection, urinary tract infection, and pneumonia), graft- and kidney function will be analysed on day 0, within the first week after LT, and 1, 3, 6, 9 and 12 months after LT.Immediately before LT and on postoperative day (POD) 3, 5, and 7, the patients’ immune status will be determined by the measurement of their HLA-DR status with the BD Quantibrite™ HLA-DR/monocyte test. The patients’ liver functions will be evaluated with the LiMAx test prior to LT and on POD 1, 3, and 7 (Figure 1).

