### Statistical methods

This exploratory data analysis will be performed calculating appropriate summary measures for the empirical distribution of the parameters. Correlation coefficients, such as the Spearman Coefficient, will be determined in connection with the MELD-score and all other correlations will be expressed using the Pearson Correlation Coefficient. The comparison of infection rates between the two groups will be analyzed using the chi-squared test. Continuous parameters will be analyzed using the *t*-test. Resulting p-values will be interpreted descriptively.

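### The primary objective concerns infection under pre-existing reduced immune competence, but no stated analysis relates HLA-DR, the study's own measure of that competence, to infection

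*Protocol article*

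**What the plan says.** All references are to the protocol article.

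- **Objective** (Study objectives, opening sentence): "The primary objective is to evaluate the rate of infectious complications in the surrounding of pre-existing reduced immune competence in patients after LT". The regimen named there is the standard tacrolimus-based one.
- **Marker** (Background): "A decreased monocytic HLA-DR status is indicative of an impaired immune competence". The same section cites a 20-patient series in which "a decreased monocytic HLA-DR status was associated with the risk of sepsis after LT".
- **Timing of the marker** (Design and trial flow): "Immediately before LT and on postoperative day (POD) 3, 5, and 7". A pre-existing value is therefore collected.
- **HLA-DR analyses** (Study objectives, secondary parameters): correlations among "preoperative HLA-DR statuses, MELD-scores and liver functions measured by the LiMAx-Test", and between postoperative HLA-DR and LiMAx. The Abstract adds a comparison of immune status between the MELD ≤20 and >20 groups.
- **Infection analysis** (Statistical methods): "The comparison of infection rates between the two groups will be analyzed using the chi-squared test". The groups are the two MELD groups of 25. Study objectives places this comparison in the paragraph on secondary parameters.
- **Link between MELD and immune competence** (Background): "it has been hypothesized that high-MELD recipients have decreased immune competence". The Discussion first says there is evidence for the link, and in its summary returns to calling it a hypothesis.

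**The concern.** The study collects both halves of its primary question, a pre-transplant measure of immune competence and the later infections, but the stated analyses do not bring them together. MELD group stands in for immune competence instead.

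That substitution has two weaknesses. The link between MELD and HLA-DR is itself under examination in this study. MELD is also built from creatinine, bilirubin and INR, so a difference in infection between MELD groups could reflect renal or hepatic disease rather than immune competence. In the other direction, if MELD and HLA-DR are only moderately related, a real association between HLA-DR and infection could leave little trace in the MELD comparison. The Discussion says that a randomised trial might follow from the results, so it matters what the infection result can be attributed to.

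**Working it through.** **1. Which pairs of variables are analysed?**

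| Pair | Stated? | Where |
|---|---|---|
| Preoperative HLA-DR with MELD | yes | Study objectives (secondary) |
| Preoperative HLA-DR with LiMAx | yes | Study objectives (secondary) |
| Postoperative HLA-DR with LiMAx | yes | Study objectives (secondary) |
| Immune status by MELD group | yes | Abstract |
| Infection by MELD group | yes | Abstract, Study objectives, Statistical methods |
| HLA-DR with infection | no | – |

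The article gives no power figure to reproduce: the 50 patients rest on feasibility, with no alpha, power or effect size. The rest of this check is illustrative.

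**2. What the proxy costs (simulation).** From the article: n = 50, 25 per MELD group, and the 85% early-infection rate. Assumed: two-sided alpha 0.05, MELD and low HLA-DR bivariate normal with correlation ρ, 25 patients drawn from each side of the MELD median, and logit P(infection) = a + ln(OR) × (SDs of lower HLA-DR). The uncorrected chi-squared test by MELD group is set against a likelihood-ratio test of HLA-DR in a logistic model.

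| Infected | OR per SD | ρ | Chi-squared by MELD group | Logistic on HLA-DR |
|---|---|---|---|---|
| 50% | 2.5 | 0.3 | about 12% | about 82% |
| 50% | 2.5 | 0.5 | about 23% | about 85% |
| 50% | 2.5 | 0.7 | about 39% | about 84% |
| 50% | 2.0 | 0.3 | about 10% | about 63% |
| 85% | 2.5 | 0.3 | about 8% | about 57% |

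Hand check of the first row: the two halves of a normal MELD distribution differ by 2 × 0.798 = 1.596 SD, so mean HLA-DR differs by 0.3 × 1.596 = 0.48 SD. The log odds ratio between groups is about 0.48 × ln 2.5 = 0.48 × 0.916 = 0.44, or OR 1.55. Around 50% infected that is roughly 55.5% against 44.5%, 11 points. The standard error is √(2 × 0.555 × 0.445 / 25) = 0.141, so z = 0.11 / 0.141 = 0.78 and power is Φ(0.78 − 1.96) + Φ(−0.78 − 1.96) ≈ 0.12.

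**3. The same point without a model.** Assume 70% infected with low and 40% with normal HLA-DR, and let a be the share of each MELD group whose HLA-DR status matches its label. The group difference is (2a − 1) × 30 points.

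- a = 1.0: 30 points, power 0.57
- a = 0.8: 18 points, power 0.24
- a = 0.6: 6 points, power 0.06

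**4. What the direct analysis can deliver.** The smallest standardised HLA-DR difference between infected and uninfected patients detectable with 80% power is (1.96 + 0.84) × √(1/n₁ + 1/n₀).

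- 50% infected (25 v 25): 2.80 × √(0.040 + 0.040) = 0.79
- 85% infected (42 v 8): 2.80 × √(0.024 + 0.125) = 1.08

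For precision, the standard error of the log odds ratio per SD near the null is about 1/√(n p(1 − p)). At 50% infected it is 1/√12.5 = 0.28, so the 95% CI multiplies and divides the estimate by e^(1.96 × 0.28) ≈ 1.7. At 85% it is 1/√6.375 = 0.40, a factor of about 2.2. Only large effects would stand out.

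**The case against.** The strongest reply is that the objective is a rate in a setting. The phrase joining infection to immune competence can mean no more than that; the Discussion uses it in this way of renal function and multi-morbidity. The aim at the end of the Background speaks of the regimen, not of an HLA-DR effect. On this reading, summary rates and the MELD comparison answer the objective. This stands as a possible reading, so it would be too strong to say that the objective goes unanswered. But the setting is still reduced immune competence, and the stated analyses identify it only by MELD.

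Second, MELD >20 is a reasoned proxy: the Discussion cites evidence for it, and immune status and infection are both compared across the same groups. This also stands. A reader might infer that HLA-DR is used only in the correlations with MELD and LiMAx; the Abstract shows otherwise. Yet two separate comparisons across MELD groups do not show whether the patients with low HLA-DR are the ones who become infected.

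Third, the list of methods is short and loosely worded, and a full protocol or SAP might add the model. The mention of other correlations is indeed open, but Study objectives spells out the HLA-DR correlations and infection is not among them. The point concerns the fit between a stated objective and the stated analyses, not a missing detail.

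Fourth, the power figures rest on assumed effects. This is correct. At 85% infected, direct logistic regression falls to about 57% at OR 2.5, 40% at OR 2.0 and 18% at OR 1.5. The direct analysis would often miss a real effect too, although it did better than the MELD comparison in every scenario tabulated above.

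**Conclusion.** The mismatch is real and should be fixed. No stated analysis relates the study's own marker of immune competence to infection, and the only infection comparison uses a proxy that the study is itself examining. Under the assumptions above (OR 2.5 per SD, correlation 0.3, alpha 0.05), the proxy comparison detects a real HLA-DR effect about 12% of the time against about 82% directly at 50% infected, and about 8% against 57% at 85%. The effect size, the correlation and the 50% rate are assumptions; only the 85% comes from the article.

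The design limits the severity: this is an exploratory pilot with p-values read descriptively. Three stronger readings are not supported.

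- A reader might infer that the study would falsely conclude that HLA-DR and infection are unrelated. Nothing commits it to drawing that from a null MELD comparison.
- A reader might take the Background to say that infection lowers HLA-DR. It links low HLA-DR to sepsis risk and suggests that it may explain reduced monocyte function during sepsis; it does not state that direction.
- A reader might infer from the Abstract, which gives HLA-DR sampling as "On the postoperative days 3, 5 and 7", that no preoperative sample is taken. Study objectives and Design and trial flow both specify one, so the difference is editorial.

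**What to change.** In Statistical methods, add as the exploratory analysis for the primary objective a logistic regression of infection (yes/no within one fixed window after transplantation, chosen before the data are examined) on preoperative HLA-DR as a continuous variable. Report the odds ratio with its 95% CI, and keep the MELD-group comparison beside it. If HLA-DR from POD 3, 5 or 7 is also related to infection, count only infections that start after the measurement, so that the marker precedes the outcome.

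If the HLA-DR question is not intended as primary, reword the objective to infection by MELD group; that also removes the mismatch.

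As an editorial correction, add the preoperative HLA-DR measurement to the Abstract to agree with Design and trial flow.

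Cost: one extra model and some wording, with no new patients, samples or visits. The downside is an imprecise estimate at n = 50, which is why the interval, rather than a p-value, should be the main output.

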### Design and trial flow

For participation in this prospective, mono-centric observational study, informed written consent is mandatory. We will evaluate 50 patients, including 25 consecutive patients with a calculated pretransplant MELD-score of >20 and 25 consecutive patients with a calculated pretransplant MELD-score of ≤20. Infectious complications (CMV-reactivation, wound infection, urinary tract infection, and pneumonia), graft- and kidney function will be analysed on day 0, within the first week after LT, and 1, 3, 6, 9 and 12 months after LT.Immediately before LT and on postoperative day (POD) 3, 5, and 7, the patients’ immune status will be determined by the measurement of their HLA-DR status with the BD Quantibrite™ HLA-DR/monocyte test. The patients’ liver functions will be evaluated with the LiMAx test prior to LT and on POD 1, 3, and 7 (Figure 1).

**Figure 1 F1:**
[figure not shown]
Flow chart of the IMUTECT study. HLA-DR= Human leukocyte antigen DR, LiMAx= Maximal liver function capacity based on ^13^C-Methacetin kinetics, LT= Liver transplantation, MELD= Model for end-stage liver disease, POD= Postoperative day.

### Sample size calculation

This is an observational pilot study. Therefore, no sample size calculation was performed. The sample size of 50 patients is resulting of the feasibility of patient recruitment within one year.

### Documentation and data handling

Protocol-required information will be documented in the case report form and reviewed and signed by the investigator or by a designated sub-investigator.

### Statistical methods

This exploratory data analysis will be performed calculating appropriate summary measures for the empirical distribution of the parameters. Correlation coefficients, such as the Spearman Coefficient, will be determined in connection with the MELD-score and all other correlations will be expressed using the Pearson Correlation Coefficient. The comparison of infection rates between the two groups will be analyzed using the chi-squared test. Continuous parameters will be analyzed using the *t*-test. Resulting p-values will be interpreted descriptively.

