## Discussion

The MELD-score was initially designed to estimate the prognosis of survival after TIPS [1]. Nowadays, it is one of the key scores used for assessing patients’suitability for a liver graft by focusing on the patient’s serum creatinine, bilirubin, and the INR ratios. The MELD-score values usually range between 6 and 40. Liver allocation follows the “sickest-patient-first” strategy, which has significantly decreased outcome after LT in Germany [17] and increased total costs associated with transplantation [18].

Advagraf® is a Tacrolimus derivate that must be taken once daily (in contrast to Prograf® which has to be administered twice per day). Blood levels of Advagraf® are usually increasing during the first week until the aimed Tacrolimus trough levels are reached.

There is evidence that the immune systems of high-MELD patients are compromised per se, which in turn, may lead to an increased risk of early infectious complications. Almost 85% of patients become afflicted with early infections, which is the most common cause of death soon after LT [15].

Additionally, poor renal function often occurs in high-MELD patients in the surrounding of multi-morbidity and as creatinine levels became a key parameter in the allocation of liver grafts. Early renal dysfunction after transplantation has been reported in up to 50% of patients [19,20]. CNI are well documented as major risk factors for early renal impairment and are believed to be responsible for chronic renal failure after LT [15]. Renal function seems to play a key role in the long-term survival of patients with higher MELD-scores, therefore, new immunosuppression strategies are necessary in order to avoid CNI-related impairment of the kidney function after LT.

There are several reported strategies aimed at forestalling renal impairment. One investigated method, the “Bottom-up” immunosuppression regime as described by Schnitzbauer *et al.,* documented the use of low dosages of immunosuppressants immediately after LT. The drug dosages were then increased in case of organ rejection or when patients were stable beyond day 30 [15].

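### The only test named for comparing infections between MELD groups, a chi-squared test, uses neither onset time nor repeat infections and cannot separate infection risk from early death; time to first infection would be a cheap improvement

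*Protocol article*

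**What the plan says.** Under Study objectives, infection is the main outcome: "The primary objective is to evaluate the rate of infectious complications". The same section plans a comparison over time: "Furthermore infection rate, graft- and kidney function over time will be analysed and compared between the two groups". Design and trial flow gives the schedule. Infections, graft function and kidney function "will be analysed on day 0, within the first week after LT, and 1, 3, 6, 9 and 12 months after LT". It also gives the groups: "We will evaluate 50 patients, including 25 consecutive patients with a calculated pretransplant MELD-score of >20", with 25 at or below that score.

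Statistical methods then names the method: "The comparison of infection rates between the two groups will be analyzed using the chi-squared test". It states no window for that test, and no time-to-event or event-count method appears anywhere in the article. The analysis is exploratory: "Resulting p-values will be interpreted descriptively". Under Sample size calculation, "Therefore, no sample size calculation was performed".

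The Discussion supplies the clinical background: "Almost 85% of patients become afflicted with early infections, which is the most common cause of death soon after LT". It also says that sickest-first allocation has worsened outcome after transplantation in Germany, but gives no mortality figure for either MELD group.

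**The concern.** The objectives ask how infection develops over a year in two groups that differ in how ill they are. The named test answers a narrower question: do the proportions of patients with an infection differ? Three kinds of information are lost.

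- **Onset time.** A pneumonia on day 4 and a urinary tract infection in month 11 count the same.
- **Repeat infections.** A patient with one infection and a patient with five count the same.
- **Death.** A patient who dies without a listed infection has left the risk set. In the two-by-two table this patient looks like one who lived the year free of infection.

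The third loss affects interpretation. The groups are split by severity of illness, so time at risk may well differ between them. A lower proportion infected in the high-MELD group could then mean fewer infections or simply earlier death, and the test cannot say which.

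**Working it through.** The article states no power, alpha or effect size, so there is no planned figure to reproduce. The calculations below are illustrations.

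**Inputs from the article:** 25 patients per group; follow-up to 12 months; early infection risk of almost 85%.

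**Assumed inputs:** mortality by group, infection hazards, independence of death and infection in the basic model, two-sided alpha of 0.05.

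**1. Effect of death before infection.** With constant infection hazard λ and infection-free death hazard μ per year,

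P(infected by 12 months) = λ/(λ+μ) × [1 − exp(−(λ+μ))].

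Take λ = −ln(0.5) = 0.693 in both groups, so the true hazard ratio is 1.

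- High MELD, mortality 30%: μ = −ln(0.7) = 0.357, giving 0.693/1.050 × (1 − 0.350) = 0.429.
- Low MELD, mortality 10%: μ = −ln(0.9) = 0.105, giving 0.693/0.799 × (1 − 0.450) = 0.477.

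With equal hazards the proportions are 43% and 48%. Putting μ in place of λ in the numerator gives death before infection: 0.357/1.050 × 0.650 = 22% and 0.105/0.799 × 0.550 = 7%. Shown beside the infection curve, these figures reveal why the first pair differs.

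With a true hazard ratio of 1.3 (λ = 0.901 in the high-MELD group), the high-MELD proportion is 51%, against 59% without death (1 − 0.5^1.3). The comparison is then 51% versus 48%.

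**2. Range when infections are front-loaded.** Hazards are now constant within month 1 and within months 2 to 12. Infection risk without death is 40%, 60% or 85%, with 30%, 60% or 90% of the infection hazard in month 1. Infection-free death risk is 10%, 20% or 30% in month 1 plus 10% later for high MELD, and 3% plus 3% for low MELD.

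- Equal infection hazards: the high-MELD proportion is lower by 1.5 to 17.6 percentage points.
- At 85% risk with 90% of the hazard in month 1, the gap is 2.5, 6.0 and 9.7 points for the three early death risks.
- True hazard ratio 1.5 at 85% risk: the difference without death is +9.2 points (94.2% − 85%). The observed difference runs from +7.1 to −8.3 points.

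The difference is attenuated in every scenario and reversed only in some.

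**3. When deaths follow infection.** Return to 30% versus 10% mortality with equal infection hazards, 85% infection risk and 90% of it in month 1.

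| Timing of deaths | High vs low, all deaths independent of infection | Gap | Gap if half the death hazard is infection-related |
|---|---|---|---|
| Even over the year | 83.6% vs 84.6% | 1 point | about 0.5 points |
| Half the death hazard in month 1 | 79.2% vs 83.2% | 4 points | about 2 points |

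Patients who die after a listed infection are already counted as infected, so the gap goes to zero as infection-free deaths disappear.

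**4. The ceiling.** At 85%, only 25 × 0.15 = 3.75 uninfected patients are expected per group. Chi-squared power is exact (uncorrected test, n = 25 per group). Log-rank power uses Schoenfeld's formula, Φ(√(d/4) × ln HR − 1.96), where d is the number of events. Deaths are ignored.

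| Proportions infected | Hazard ratio | Events | Chi-squared | Log-rank |
|---|---|---|---|---|
| 85% vs 97.75% | 2.00 | 45.7 | 35% | 65% |
| 92% vs 78% | 1.67 | 42.5 | 30% | 39% |
| 50% vs 30% | 1.94 | 20.0 | 33% | 32% |

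For the first row, d = 25 × (0.85 + 0.9775) = 45.7 and √(45.7/4) × 0.693 − 1.96 = 0.38, giving 0.65. The gain is large near the ceiling and absent at moderate risk.

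**The case against.** The strongest reply is that the chi-squared test is not invalid. With complete follow-up, the proportion ever infected by 12 months is exactly the cumulative incidence of infection with death as a competing event. An Aalen–Johansen curve would end at the same 43% and 48%. The figures without death describe a hypothetical population in which nobody dies. This stands. A reader might infer that the test requires every patient to be at risk for the whole window; it does not. The point is which quantity is estimated and how it will be read.

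The mortality inputs are also assumed, and the Discussion's link between early infection and early death works against the mechanism, as step 3 shows. This stands too, and makes the direction conditional.

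Three further inferences are tempting but unsupported:

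- **Repeated testing.** The schedule lists when outcomes are analysed. It does not prescribe a chi-squared test at each time, and Statistical methods gives no window. A single 12-month proportion and a test at each time are both possible readings, and with descriptive p-values no error rate is claimed.
- **A bias in favour of the study's hypothesis.** The Discussion expects more early infections in high-MELD patients, so attenuation works against that expectation. The hoped-for benefit of low-dose over standard regimens cannot be tested in a single-regimen comparison by any method.
- **Missing onset dates or rules for deaths.** The case report form is not shown, and an article may leave such detail to the full protocol. The point rests on the test that the article does name.

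Finally, power matters little in a pilot sized by feasibility. That lowers the severity but leaves the problem of interpretation.

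**Conclusion.** The point holds in a limited form. The one method named for the infection comparison does not match the stated aim of comparing infection over time to 12 months: it discards timing and repeat events and cannot distinguish fewer infections from earlier death.

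If infection-free death is more frequent in the high-MELD group, the proportion infected understates that group's infection hazard. Under the scenarios in step 2 with equal infection hazards, the understatement relative to low MELD is 1.5 to 17.6 points; it approaches zero if early deaths mostly follow infection. A reader might infer that the high-MELD group will look less infected than it is. The documents do not establish this, because they give no mortality by MELD group.

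The loss of power is material only near the quoted 85% risk. Since the study is an exploratory pilot with descriptive p-values, this is a cheap improvement of low severity.

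**What to change.** - Name one main window for the infection comparison.
- Analyse time to first listed infection from onset dates, with a cause-specific hazard ratio for MELD above 20 versus 20 or below and its 95% CI.
- Show cumulative incidence curves by group for infection and, beside them, for death before infection. The infection curve alone would repeat the 12-month proportion; the hazard ratio and the death curve make it interpretable.
- As a supportive analysis, report infections per patient-time at risk, so that repeat infections count.
- Keep the chi-squared test as a simple descriptive comparison for the first-week window.

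The cost is some extra analysis, an onset-date field if none is collected already, and effect measures that are less familiar than proportions. With 25 patients per group the intervals will be wide, which suits a descriptive report.
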